## Abstract

**Background:**

Patellofemoral complaints are frequently seen in younger and active patients. Clinical strategy is usually based on decreasing provoking activities as sports and demanding knee activities during work and leisure and reassuring the patient on the presumed good outcome.

Exercise therapy is also often prescribed although evidence on effectiveness is lacking.

The objective of this article is to present the design of a randomized clinical trial that examines the outcome of exercise therapy supervised by a physical therapist versus a clinically accepted "wait and see" approach (information and advice about the complaints only).

The research will address to both effectiveness and cost effectiveness of supervised exercise therapy in patients with patellofemoral pain syndrome (PFPS).

**Methods/design:**

136 patients (adolescents and young adults) with patellofemoral pain syndrome are recruited in general practices and sport medicine centers. They will be randomly allocated receiving either 3 months of exercise therapy (or usual care.

The primary outcome measures are pain, knee function and perception of recovery after 3 months and 12 months of follow up and will be measured by self reporting.

Measurements will take place at baseline, 6 weeks, and 3 monthly until 1 year after inclusion in the study.

Secondary outcome measurements include an economic evaluation.

A cost-utility analysis will be performed that expresses health improvements in Quality Adjusted Life Years (QALYs) and incorporates direct medical costs and productivity costs

**Discussion:**

This study has been designed after reviewing the literature on exercise therapy for patellofemoral pain syndrome. It was concluded that to merit the effect of exercise therapy a trial based on correct methodological concept needed to be executed.

The PEX study is a randomized clinical trial where exercise therapy is compared to usual care. This trial started in April 2005 and will finish in June 2007. The first results will be available around December 2007.

## Background

Patellofemoral pain syndrome (PFPS) is a common complaint in adolescents and younger adults. Though exact epidemiological data do not exist, 5–6 six new cases per year in Dutch GP-practices may be expected [1]. The symptom most frequently reported is a diffuse peripatellar and retropatellar localized pain, typically provoked by ascending or descending stairs, squatting, cycling and sitting with flexed knees for prolonged periods of time [2,3]. Weakness of the knee extensors and abnormal firing patterns of the nerves innervating these knee extensors have been found in patients with PFPS. These phenomena are thought to cause maltracking of the patella through the femoral groove, resulting in increased intrapatellar pressure. Tight anatomical structures and heavy physical loading may add to the pressure. This pressure probably causes patellofemoral pain.

PFPS frequently becomes a chronic problem, forcing the patient to stop sports and other similar activities [4]. The long-term prognosis is generally more favorable for young patients, but seems to be independent of the presence of cartilage damage or gender [5].

Clinical guidelines of the Dutch College of General Practitioners [6] advise GPs to inform the patient about the background of the condition and its favorable prognosis. Patients are advised to refrain from all (sports-) activities that provoke pain, and to find alternative exercises to keep in shape. Non-weight bearing quadriceps strengthening exercises may be considered, but the guidelines explicitly mention that evidence for its effectiveness is lacking. Patellar taping is not advised. In case of prolonged unresponsive, severe complaints, referral to an orthopedic surgeon may be considered. General practitioners do not always adhere to these guidelines and prescriptions for analgesics such as paracetamol and NSAIDs to reduce pain and referrals to physical therapists (exercise therapy) are among the treatments regularly encountered (unpublished data authors). People involved in sports and athletic activities may consult sports clinics with their symptoms. In sports clinics it is more common to refer to physical therapy for exercises (unpublished data authors).

Evidence for the effectiveness of conservative therapies for PFPS is scarcely available [2]. Exercise therapy is based on the theoretical assumption that muscle weakness or imbalance is a major contributor in the development of PFPS. The recent Cochrane review [7] performed by our group identified only 3 trials comparing exercise therapy with a control group not receiving exercise therapy

We found limited evidence that exercise was beneficial, though the quality of the trials was such that further research was recommended to confirm this conclusion [7]. Recently a small placebo controlled trial was published investigating the short-term effectiveness of exercise therapy combined with taping and passive manual mobilization of the patella. The control group received sham ultrasound and placebo-taping. The authors reported beneficial effects in the intervention group (n = 33) compared the control group (n = 34) after 6 weeks follow-up [8]. Cost effectiveness data are not available at all.

Because physicians, especially the GP and sports physician, frequently are confronted with patients with PFPS, but by lack of evidence are unable to apply the most (cost)effective treatment, a randomized intervention study is highly indicated. The 'wait and see' policy advocated in the guidelines should be compared to the more active approach of exercise therapy under supervision of a physical therapist, in order to assess (cost)effectiveness of both approaches.

The trial will target patients (adolescents and young adults) presenting in general practice and sports clinics with the symptoms of PFPS and no history of previous active treatment with exercises.

In this article we will present the detailed protocol of the trial.

This trial started April 2005 and patients will be included until June 2006.

## Methods/design

### Study design

This study is a randomized clinical trial to study short-term and long-term (cost) effectiveness of exercise therapy in combination with advice and information on the background of PFPS compared to advice and information on the background of PFPS only ("wait and see")

The study design (Figure 1) was approved by the Medical Ethics Committee at the Erasmus MC – university medical centre Rotterdam. All patients gave written informed consent.

### Patient selection

Patients eligible for this trial are adolescents and young adults in the age of 14 to 40 years consulting the GP or sports physician for PFPS lasting longer than two months but not longer than 2 years. Recruitment will take place in "HONEUR" practices (a research network of 38 general practices allied with the Department of General Practice of Erasmus MC) and in 4 sports medical centers in Rotterdam, Leidschendam, Breda and Gorinchem.

The recruitment period is planned from April 2005 until June 2006.

### In- and exclusion criteria

Inclusion criteria are the following diagnostic criteria;

Presence of at least 3 symptoms of the following: pain when walking stairs, pain when squatting, pain when running, pain when cycling, pain when sitting with knees flexed for a prolonged period of time, grinding of the patella, positive physical tests (Clarke's test, Rabot sign, patella release test).

The exclusion criteria are: knee osteoarthrosis/arthritis, previous knee injury or knee operations, patellar tendinopathy, M. Osgood Schlatter, or other defined pathological conditions of the knee.

### Sample size

Sample size is based on studies included in our systematic review [7]. In a single study investigating a similar contrast of interventions [9] there was an absolute increase in recovery of 22% (19% recovery in the usual care group to 41% recovery in the exercise therapy group) after one year, OR 2.21 (95%CI 0.87 – 5.64)). This represents a clinically relevant increase and is expected to be even more pronounced after 3 months follow-up. Such a difference can be detected statistically (power 0.80, alpha 0.05 one-sided test) with 61 patients per group. With a potential dropout rate of 10% a total of 136 patients should be included.

### Intervention

The interventions that will be compared in this trial are:

A) Exercise therapy for a period of 6 weeks, provided by a physical therapist according to a standardized protocol drawn up according to present international expert opinion and modified by local participating physical therapists into a practical protocol which is feasible in daily practice. The program consists of static and dynamic muscular exercises for quadriceps muscles, balance exercises and flexibility exercises. Patients are directed to practice 7 times a week during 20 minutes.

Instructions concerning the exercises will be noted on the "workout book" (Figure 2) which has been designed for the study. The notes regarding frequency and duration of exercises is send to the investigators after the three month period of exercise.

Patients will receive standardized information about the background and prognosis of PFPS on a specially designed leaflet. After the period of 6 weeks patients will be advised to keep up the exercises at home for the following 6 weeks.

B) The control group will receive the standardized information and advice. This advice consists of the information usually given by GPs, according to the guidelines: information about the background of the condition and its good prognosis, advice to refrain from all (sports-) activities that provoke pain, and to find alternatives to keep in shape.

An information leaflet for the patients has been compiled to contribute to the standardization for both groups.

#### Co-interventions

During the one year follow-up other interventions like the use of ice applications, bandages or braces, or consumption of oral analgesics (NSAIDs or paracetamol) indicated by pain severity are allowed for both groups. Information about these co-interventions will be collected after 6 weeks and every 3 months and during one year follow-up and will be used in the cost-effectiveness analysis.

### Randomization

After recruitment through the participating GP's and sport physicians the patient is finally accepted in the study after written informed consent and reassessment of the inclusion and exclusion criteria.

Following this informed consent and baseline assessments, patients are allocated to the intervention or control group using a blinded and computer based randomization list.

The randomization table will be stratified for the setting (general practice versus sports clinic) and for age (14–18 versus 19–40). Patient are informed about the treatment allocation and subsequently the patients in the exercise group receive their treatment from a physical therapist in a predetermined centre, whereas patients in the control group will not receive this intervention.

### Measurements

#### Outcome parameters

Primary outcome measures are: perceived recovery (measured with a 7 point Likert scale [10] functional disability using a disease-specific disability scale (Kujala Patellofemoral Scale) [11] and a pain severity using a numerical rating scale[12] after 3 and 12 months of follow-up. (Table 1)

Secondary outcome measures are cost-effectiveness after one year, the primary outcome parameters at 6 weeks follow-up, quality of life (Euroqol)[13] and a numerical rating scale (NRS 0–10) for difficulties encountered during work, school or sports activities. Medical consumption (visits to health care providers and consumptions of prescription or over the counter medication), absence from work or decreased productivity at work, and other indirect an direct costs are all included in the economic evaluation.

Baseline and follow-up questionnaires at 6 weeks and 3 and 12 months will be filled out by the patients themselves. Quality of life, direct costs and productivity costs and compliance to the interventions will be measured after 6 weeks and every 3 months during one year also by self report.

### Analyses

All analyses will take place after the trial has finished, no intermediate analyses will be performed.

To evaluate the effectiveness of supervised exercise therapy in patients with PFPS differences in clinical outcome measures between intervention and control group will be analyzed on the basis of intention to treat. Additionally, analysis per protocol will be conducted. Dichotomous outcomes at three and 12 months follow-up will be analyzed using logistic regression techniques and continuous outcomes with linear regression techniques. Of the primary outcomes perceived recovery will be dichotomized to recovered (fully, strongly) or not recovered (slightly-strongly worsened). Other primary outcome measurements will be analyzed as continuous variables

Analyses will be adjusted for baseline values and for co-interventions and possible prognostic factors in case the effect estimate changes with more than 10% when including these variables in the model.

Additionally the overall one year dichotomous outcomes will be analyzed using GEE (generalized estimating equations) [14], continuous outcomes will be analyzed using linear regression for repeated measurements. Both techniques take the correlation of multiple measurements within one patient into account.

Research question 2 "What is the cost-effectiveness of supervised exercise therapy in patients with PFPS...." is the basis for the economic evaluation.

In the economic evaluation (a cost utility analysis) both the costs and the consequences of both treatment options are compared and incremental costs and incremental health effects the latter (in terms of quality of life) is estimated.

The economic evaluation is performed alongside the randomized clinical trial. Patients will complete questionnaires for costs and quality of life after 6 weeks and every 3 months. Only if the difference in health between the treatment arms appears not to be stable over time, an additional modeling study using a Markov model will be performed. Statistical methods are used to describe uncertainty in costs and effects estimates based on patient data. A 95% confidence interval for the cost-utility ratio will be calculated and an acceptability curve will be presented

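### The clinically relevant gain in recovery is set in percentage points, but the plan names no absolute effect measure, and its 10% covariate rule can be tripped by a logistic odds ratio without confounding

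*Protocol article*

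**What the plan says.** In the protocol article, Sample size, the reference effect comes from one earlier study of a similar contrast: "there was an absolute increase in recovery of 22% (19% recovery in the usual care group to 41% recovery in the exercise therapy group"). The article comments: "This represents a clinically relevant increase and is expected to be even more pronounced after 3 months follow-up". The same sentence also gives that study's result as an odds ratio: "after one year, OR 2.21", with a 95% confidence interval of 0.87 to 5.64. The design is then "power 0.80, alpha 0.05 one-sided test) with 61 patients per group", and "With a potential dropout rate of 10% a total of 136 patients should be included".

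In Analyses, perceived recovery is cut to recovered or not recovered, and "Dichotomous outcomes at three and 12 months follow-up will be analyzed using logistic regression techniques". Models are adjusted for baseline values, and for co-interventions and possible prognostic factors, on a change-in-estimate rule: a variable is kept if including it moves the effect estimate by more than 10%. The wording leaves open whether the rule also governs the baseline values. A longitudinal model is planned too: "Additionally the overall one year dichotomous outcomes will be analyzed using GEE". No link function or effect measure is given for it. The section names neither a risk difference nor an odds ratio as the quantity to be reported for recovery.

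**The concern.** Two features of the plan do not fit together well.

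First, the yardstick for clinical relevance is a difference in percentage points, while the planned model's direct output is an odds ratio. Recovery is common at the planned rates, so an odds ratio is neither close to the risk ratio nor readable as points without knowing the control rate.

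Second, the 10% rule treats movement in the effect estimate as a sign of confounding. For a mean difference in a linear model that is reasonable, because balanced covariates leave it unchanged. For an odds ratio it is not: a covariate that predicts recovery moves the odds ratio away from 1 even when perfectly balanced between the arms.

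At stake is how a primary outcome is interpreted. The covariates in the model, and so the meaning of the reported odds ratio, would depend on the data. The rule would tend to admit variables that enlarge the odds ratio, and the 3- and 12-month estimates might not be on a common scale. None of this would tell the reader whether the 22-point gain was reached or excluded.

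**Working it through.** **Inputs.** Recovery 19% and 41%, power 0.80, one-sided alpha 0.05, 61 per group, 10% dropout (Sample size); logistic regression and the 10% rule (Analyses). The strength of the prognostic covariate is not given in the article and is assumed over a range.

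**1. The plan's own sample size.** With mean rate 0.30:

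n = [1.645·√(2·0.30·0.70) + 0.842·√(0.19·0.81 + 0.41·0.59)]² / 0.22² = (1.066 + 0.529)² / 0.0484 ≈ 52.6.

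Continuity correction: (52.6/4)·[1 + √(1 + 4/(52.6·0.22))]² ≈ 61.3, which is 61 rounded to nearest and 62 rounded up. Dropout: 61/0.9 = 67.8, so 68 per arm and 136 in total. The stated figures reproduce.

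**2. The planned effect on each scale.**
- Risk difference: 0.41 − 0.19 = 0.22.
- Risk ratio: 0.41/0.19 = 2.16.
- Unadjusted odds ratio: (0.41/0.59)/(0.19/0.81) = 2.96.

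Precision of the risk difference at 61 per group: SE = √(0.19·0.81/61 + 0.41·0.59/61) = 0.0806, so the 95% interval is 0.22 ± 1.96·0.0806, about 6 to 38 points.

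**3. Effect of a balanced covariate.** Let X be standard normal, identically distributed in both arms, with log-odds slope b. Find the intercepts a₀ and a₁ for which the average of 1/(1 + exp(−(a + bX))) over X equals 0.19 and 0.41. The conditional odds ratio is exp(a₁ − a₀). For b = 1.0, a₀ = −1.723 and a₁ = −0.440, giving exp(1.283) = 3.61.

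| b (assumed) | Conditional OR | Change from 2.96 | Change in log OR | Risk difference |
|---|---|---|---|---|
| 0.5 | 3.13 | +5.5% | +4.9% | 22 points |
| 0.75 | 3.33 | +12.3% | +10.7% | 22 points |
| 1.0 | 3.61 | +21.8% | +18.2% | 22 points |
| 1.5 | 4.42 | +49.2% | +36.9% | 22 points |

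For a 50:50 binary covariate with its own odds ratio of 2, 4 or 8 (assumed), the conditional odds ratio is 3.04, 3.28 or 3.70, a change of +2.7%, +10.8% or +24.8%. So the 10% threshold is crossed with no imbalance at all from a slope of about 0.75, or a binary odds ratio of about 4.

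**4. How often the rule would fire.** In simulated trials of 61 per arm at these rates, with one randomly distributed normal covariate, the odds ratio moved by more than 10% in about 36% of trials at b = 0.5 and about 74% at b = 1.0. In over 90% of those trials the odds ratio rose. Chance imbalance contributes here, which is why b = 0.5 triggers at all. Imbalance alone would push the odds ratio up and down about equally often, so the lopsidedness reflects non-collapsibility.

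**5. Reading an odds ratio against 22 points.** A fixed odds ratio of 2.96 means a gain of 14.8, 22.0, 25.9 or 26.4 points at control recovery of 10%, 19%, 30% or 40%. The article gives no control rate for 3 months.

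**The case against.** The strongest reply is that Analyses names a model, not an effect measure. A condensed article may leave the reported summary to a fuller document, and sizing on two proportions while testing by logistic regression is common practice. That stands: an unnamed summary measure alone would not be a finding, and the sample size is not in question. What the reply does not remove is the 10% rule, which this text does fix and which behaves badly on the odds-ratio scale.

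A reader might go further and infer that recovery is analysed only by logistic regression, or that its result cannot be set against the 22-point target. The article supports neither. A GEE analysis is also planned, and a risk difference can be obtained from the same logistic model by averaging its predicted probabilities. Nor is the reference effect purely absolute, since Sample size also quotes an odds ratio. That 2.21 differs from the 2.96 implied by 19% and 41%; the article does not explain the difference, and it may be an adjusted figure. It is a separate matter.

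It is also fair that the covariate strengths are assumed, that at a slope of 0.5 balanced non-collapsibility alone stays below 10%, and that if no variable met the rule the model could be unadjusted. Perceived recovery has no obvious baseline value of its own. Different covariate sets at 3 and 12 months are possible under the rule, not certain. Finally, whether the risk difference should replace the odds ratio as the primary measure is debatable; reporting it alongside is not.

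**Conclusion.** The concern holds in a limited form. Clinical relevance is stated as a 22-point gain, no absolute effect measure is named for recovery, and the 10% rule is unsuitable if the effect estimate it monitors is the logistic odds ratio. With the absolute gain unchanged, a balanced prognostic covariate moves that odds ratio from 2.96 to about 3.1 to 4.4, so the rule can select covariates without confounding and mostly in the direction of a larger odds ratio.

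This rests on three assumptions: that the monitored estimate is the odds ratio, which the article does not say; that at least one candidate covariate has a log-odds SD within 0.5 to 1.5; and that the recovery rates are near those planned. The weakness is specific to recovery. The linear models for pain and function are not affected in this way. It is a matter of interpretation and pre-specification that should be put right, and it does not undermine the validity of the trial or its size.

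**What to change.** Keep the logistic model. In Analyses:

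1. State that recovery at 3 and 12 months will be reported as the odds ratio together with the standardised (marginal) risk difference. Predict each patient's recovery probability under both arms, average within each arm assignment, and take the difference, with a delta-method or bootstrap 95% confidence interval. Read it against the 22 points. Do the same from the GEE.
2. In place of the 10% rule on the odds ratio, name one covariate set in advance and use it at both time points. It should consist of baseline variables, for example the stratification factors, setting and age group. Co-interventions arise after randomisation and so would not belong to it.

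The cost is two sentences and a little extra analysis work, with no new data and no change to the 136 patients. All analyses are planned for after the trial ends, so the change can be made before any outcome comparison is seen.

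### The intention-to-treat analyses may be adjusted for co-interventions that arise after randomisation, and the 10% change-in-estimate rule does not guard against the bias this can cause

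*Protocol article*

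**What the plan says.** The Analyses section sets the principle that "differences in clinical outcome measures between intervention and control group will be analyzed on the basis of intention to treat". It then gives the adjustment rule: "Analyses will be adjusted for baseline values and for co-interventions and possible prognostic factors". A condition is attached to that rule, so that the adjustment applies only "in case the effect estimate changes with more than 10% when including these variables in the model". The rule is written for the analyses in general and names no exception for the primary outcomes.

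The Co-interventions section says what these variables are and when they arise: "During the one year follow-up other interventions like the use of ice applications, bandages or braces, or consumption of oral analgesics", with the qualifier "indicated by pain severity are allowed for both groups". On their recording it says "Information about these co-interventions will be collected after 6 weeks and every 3 months". The only use it names for them is that they "will be used in the cost-effectiveness analysis".

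Two other sections matter. Under Randomization, allocation follows consent and the baseline assessments. Under Outcome parameters, the primary outcomes are perceived recovery, the Kujala score and a numerical rating of pain, at 3 and 12 months.

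**The concern.** Adjustment in a randomised trial is safe when the covariate was fixed before allocation. A co-intervention taken during follow-up was not. If exercise lowers pain, patients in that arm have less need for analgesics. Holding analgesic use constant then removes part of the effect the trial sets out to estimate. It also compares unlike patients: an exercise patient and a control patient with the same use will tend to differ in underlying prognosis, because treatment has already moved one of them. The result is neither the contrast named under Study design (exercise plus advice versus advice only) nor a clean effect with co-intervention use held fixed.

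The 10% condition is borrowed from confounder selection in observational work. In a randomised trial a post-allocation variable cannot be a confounder of allocation, so a large movement in the estimate is no reason to include it. What is at stake is the reported odds ratio for recovery and the mean differences in pain and function.

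**Working it through.** **Order of events.** Baseline assessment comes first, then allocation, then co-interventions during the year, recorded at 6 weeks and 3-monthly, with primary outcomes at 3 and 12 months. Co-interventions therefore lie between allocation and outcome, and at least one class of them is tied to pain.

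**The plan's own figures.** It gives none for co-intervention use or for the adjustment. The only figures to borrow are from Sample size: recovery of 19% versus 41%, and 61 per group. A one-sided, continuity-corrected two-proportion formula at alpha 0.05 and power 0.80 gives 62 per group against the stated 61, and 122/0.9 = 135.6, that is 136. These only set the scale of the simulations below. Everything else in them is assumed.

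**Check 1: recovery, large sample.** Recovery means that a normal latent severity falls below a threshold set to give 19% versus 41%. The exact odds ratio is (0.41/0.59)/(0.19/0.81) = 2.96. Use of a co-intervention follows a logistic model in severity, with 43% use in the control arm, and has no effect of its own on recovery. The odds ratio with the co-intervention in the model is compared with the one without it.

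| Log-odds slope per SD of severity | Shift of the odds ratio toward 1 |
|---|---|
| 0.3 | 1% |
| 0.5 | 3% |
| 0.8 | 6% |
| 1.2 | about 10% |
| 2 | 18% (2.94 to 2.42) |

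A slope of 2 is strong: exp(2) = 7.4 in odds per SD, with use of about 4% in recovered and 47% in non-recovered patients. The 10% threshold is reached at about exp(1.2) = 3.3 per SD.

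**Check 2: pain, large sample (n = 400,000).** Baseline pain P0 is N(6, 1.5) and U is an unmeasured N(0, 1) prognostic factor. A is 1 for exercise and 0 for control. Pain at about 6 weeks is P1 = 0.5·P0 + U − A + error. Use C has logit −1 + b(P1 − 3). Later pain is Y = 0.5·P1 + 0.5·U − 0.5·A + g·C + error. With C held fixed, the effect of exercise is 0.5(−1) − 0.5 = −1 by construction.

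| b | g | Use, control v exercise | Baseline-only estimate | With C added | Change |
|---|---|---|---|---|---|
| 0 | 0 | 27% v 27% | −1.00 | −1.00 | 0% |
| 0.3 | −1 | 28% v 22% | −0.94 | −0.97 | 3% away from null |
| 0.6 | 0 | 30% v 20% | −1.01 | −0.93 | 8% toward null |
| 0.6 | −0.5 | 30% v 21% | −0.94 | −0.91 | 3% toward null |
| 1 | 0 | 33% v 20% | −1.01 | −0.85 | 15% toward null |
| 1 | −0.5 | 33% v 20% | −0.93 | −0.85 | 9% toward null |
| 1 | −1 | 33% v 20% | −0.87 | −0.85 | 2% toward null |

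The baseline-only model recovers the total effect. For b = 1, g = −0.5 that effect is −1 + (−0.5)(0.20 − 0.33) = −0.935. The adjusted figure of −0.85 is neither this nor the −1 that applies with use held fixed.

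**Check 3: the 10% rule at 61 per arm (3,000 replicates, same model).** The pairs give the mean estimate from the baseline-only model and the mean after the rule has chosen the model.

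| b, g | Rule fires, true effect | Baseline-only to reported | Rule fires, no effect |
|---|---|---|---|
| 0.6, −0.5 | 10% | −0.95 to −0.94 | 44% |
| 1, −0.5 | 41% | −0.94 to −0.88 | 64% |
| 1, 0 | 70% | −1.00 to −0.87 | 82% |

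With no effect, the rule fires often because 10% of a near-zero estimate is tiny. The mean stays at about zero, but chance decides which model is reported.

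**The case against.** The best reply is that the adjustment is conditional. A reader who stops at the first half of the sentence might infer that co-interventions will always be in the model, and the text does not say so. The comparison also requires an estimate without them, so that estimate will exist. This stands, but the rule then calls for the adjusted analysis whenever the two differ by more than 10%, and no baseline-only model is named as primary.

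A second reply is that the shift may be small. This also stands. It is negligible if use hardly depends on severity, and in most settings of Check 2 it shrinks when the co-intervention itself relieves pain. The 18% needs a strong dependence.

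A third concerns the qualifier about pain severity, which may grammatically attach only to oral analgesics. I rely on it only for those. Ice, bandages and braces remain post-randomisation variables in any case.

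Two stronger readings are tempting but not supported. One is that the rule fires exactly when a variable lies on the causal pathway. A moderate case of Check 1 moves the odds ratio from 2.98 to 2.77, or 7%, so a variable affected by treatment stays out. Conversely, the rule fires often when there is no effect and so no pathway. The other is that adjustment creates an effect where none exists. A simulation does turn an odds ratio of 1.0 into 0.84 or 0.75, but only if exercise cuts use (35% to 21%, or to 13%) without changing severity. The article gives no basis for that, and both results run against exercise. Where use follows severity alone and exercise has no effect, no bias appeared.

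**Conclusion.** The concern holds as a flaw in a stated rule. The protocol article allows variables that arise after allocation, at least one of them driven by a primary outcome, into models it calls intention to treat. The rule that admits them has no means of telling harm from help. Where the shift is small the covariate is unnecessary; where it is large, inclusion can distort the estimate.

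The size is about 0 to 18%, mainly toward no effect. This rests wholly on the assumed dependence of use on severity and the assumed effect of the co-intervention. A reader might infer that the primary results will be biased; the documents support only that they can be.

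**What to change.** In the Analyses section:

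- Remove co-interventions from the covariates of all intention-to-treat models, including the repeated-measures ones, and apply the 10% rule to no variable measured after randomisation.
- Adjust the primary models only for prespecified variables measured before randomisation: the baseline value of the outcome and the stratification factors, setting and age. This also stops the data from choosing prognostic covariates for those models.
- Report co-intervention use by arm, and keep it in the cost analysis as the Co-interventions section already intends.
- Label any model adjusted for co-interventions as exploratory.

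The cost is a sentence or two of text. No new data are needed, and the sample size of 61 per group and 136 in total is unchanged.
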